#### 2.13.2. Measurement Bias

At each visit, the measured parameters are documented in the case report forms (CRFs). In addition, all patients will be followed-up after screening and implantation of the Impella CP^®^ system. Finally, monitoring (on-site and central) will be carried out during the trial by staff of the Department of Cardiology and of the Center for Clinical Studies, Jena University Hospital.

### 2.14. Treatment Compliance/Drop-Out Rate at Follow-Up

Treatment compliance is not influenced by the patient as the patient is normally unconscious and in a critical clinical condition. As a result, 100% treatment compliance is assumed. Loss of follow-up is estimated to be less than (<4%) based on other clinical studies in cardiogenic shock [9,11,12].

### 2.15. Data Management

#### 2.15.1. Data Assessment/Case Report Forms

Paper CRF and a web application for study management software are used for data documentation (Redcap Database). The data will be stored online in REDCap (Research Electronic Data Capture, REDCap Consortium, Vanderbilt University (USA)). REDCap is a secure web application for building and managing online surveys and databases. The software meets the regulatory requirements (GCP, 21CFR Part11). The data will be entered via encrypted connection (HTTPS) in web browser input masks. Each subject will be given an unambiguous patient identification number to ensure pseudonymized data analysis. The data are verified by range, validity and consistency checks. The data manager will demand clarification of missing or implausible data from the study teams. Each change in data, e.g., due to resolved queries, will be documented in the data base by an automated audit trail. Unauthorized data access is prohibited by a hierarchical concept of access based on users and roles.

#### 2.15.2. Ethics Approval

The study was approved by the institutional review board and ethics committee of the Friedrich Schiller University (registration number: 4939-10/16).

#### 2.15.3. Privacy, Collection and Processing of Data

All data/information obtained during the study are subject to appropriate use and protection and will be treated in accordance with the comprehensive regulations of the national data protection law in strictest confidence. During the study, subjects will be identified exclusively by an individual identification code (subject number). For protection of these data, organizational procedures are implemented to prevent distribution of data to unauthorized parties. The appropriate regulations of local data legislation will be fulfilled in their entirety.

#### 2.15.4. Dissemination

All findings of this study will be published in a renowned international medical journal, regardless of the outcomes. We used the SPIRIT reporting guidelines for reporting [22].

## 3. Summary and Conclusions

Although MCS-treatment with Impella CP^®^ is an option in cardiogenic shock, data published assessing the use of Impella^®^ and its impact are too small to draw definite conclusions with regard to clinical endpoints such as unloading characteristics, hemodynamics or mortality. The only currently recruiting larger randomized clinical trial powered for clinical endpoints—DanGer-Shock—will still need several additional years until finalization [23]. The implementation of the Impella CP^®^ in patients with cardiogenic shock offers rapid improvement from circulatory failure and increases in end-organ tissue perfusion in a less invasive rescue strategy. This could be the optimal device for patients with cardiogenic shock, reducing the rate of severe bleeding events, systemic inflammatory response syndrome, or limb ischemic events. Furthermore, left ventricular performance might also be positively influenced as a result of direct cardiac unloading an antegrade, more physiological outflow into the acceding aorta. However, the Impella CP^®^ has a flow limitation of maximally 3.5 L/min (under laboratory model conditions using water) and is limited to compensation for left ventricular failure. By contrast, this technology is not able to support profound, critical states of shock with coexisting condition that need combined respiratory and (biventricular) circulatory therapy. Prospective clinical studies such as the JenaMACS trial are therefore warranted.

## Figures and Tables

**Figure 1 jcm-11-04623-f001:**
[figure not shown]
Flow chart of the study design. PAC = Pulmonary artery catheter; MAP = Mean arterial pressure; SAPS = Simplified acute physiology score; SAVE = Survival after VA ECMO; ICU = Intensive care unit; GCS = Glasgow outcome scale.

**Figure 2 jcm-11-04623-f002:**
[figure not shown]
Study set up for measuring the primary outcome after 24 h of Impella^®^ support post-implantation via PAC and TTE(Graphic generated using BioRender©).

**Table 1 jcm-11-04623-t001:** Inclusion and exclusion criteria of the JenaMACS study.

Inclusion	Exclusion
- Systolic blood pressure < 90 mmHg, >30 min of inotropic agents and/or vasopressors to keep the blood pressure > 90 mmHg systolic - Signs of left ventricular failure with pulmonary congestion. - Signs of end-organ hypoperfusion with at least one of the following criteria: - Somnolence. - Cold, pale skin or extremities. - Oliguria (≤30 mL/h). - Serum lactate > 2.0 mmol/L. - Age ≥ 18 years ≤90 years. - Signed informed consent	- Contraindications to Impella CP^®^ implantation. - Shock duration > 12 h before evaluation. - Severe PVD making Impella implantation impossible. - Aortic valve insufficiency/stenosis at least II°. - Age > 90 years. - CNS disease with fixed, dilated pupils (not drug-induced). - Severe concomitant disease with limited life expectancy < 6 months. - Participation in another study. - CPR > 30 min. - Shock due to other reasons.

CNS = Central nervous system, CPR = Cardiopulmonary resuscitation, PVD = Peripheral vessel disease.

**Table 2 jcm-11-04623-t002:** Ramp Test protocol: A ramp test will be performed 24 h after Impella CP^®^ implantation according to the following protocol.

Speed	Flow	Mean BP	HR	PCWP	Mean PA	PAO2	Lactate	CI	MR	LVEDD	LVESD	LVEF	RVEDD
	[L/min]	[mmHg]	[L/min]	[mmHg]	[mmHg]	[%]	[mmol/L]		[Degree]	[mm]	[mm]	[%]	[mm]
**P8**													
**P6**													
**P4**													
**P2**													

BP = Blood pressure; HR = heart rate; PCWP = Pulmonary, capillary wedge pressure; PA = Pulmonary artery; CI = Cardiac index; LVEDD = Left ventricular end-diastolic diameter, LVESD = Left ventricular end-systolic diameter; LVEF = Left ventricular ejection fraction; RVEDD= Right ventricular end-diastolic diameter; T = Impella flow level, MR = Mitral regurgitation.

**Table 3 jcm-11-04623-t003:** Frequency and scope of the JenaMACS study visits.

					Time Point					
Protocol Item	Pre PCI	Post-PCI	Day 1	Day 2	Day 3-X *	Stabilization ^+^	Day 7/E	30 Rays	6 M.	12 M.
Inclusion/exclusion criteria	X									
Informed consent	X									
12-lead surface ECG	X	X	X	X	X	X	X	X		
Laboratory evaluation ^∆^	X		X	X	X	X	X			
Medical history, Comorbidities ^∆^	X									
Physical examination ^∆^	X	X	X	X	X	X	X	X	X	X
BGA including lactate	X	X	X	X	X	X				
Creatinine clearance **	X		X	X	X					
Blood Samples (Measurement of biomarkers)	X	X	X	X	X	X	X	X	X	X
PAC—Hemodynamics	X	X	X	X	X	X				
Measurement of parameters of hemodynamics ^∆^	X	X	X	X	X	X				
TTE	X	X	X	X	X	X	X	X		
Dose of isotopes and vasopressors	X	X	X	X	X	X	X	X		
Impella CP^®^ data	X	X	X	X	X	X				
SAPS-II Score		X	X	X	X	X				
CCS category								X	X	X
NYHA category								X	X	X
Quality of Life (EQ-5D)							X	X	X	X
Measurement of the neurological outcome (GCS) ^∆^	X	X	X	X	X	X	X	X	X	X

^∆^ Data documentation from clinical routine (if available), * every day until hemodynamic stabilization; ** Clearance calculated according to Cockcroft-Gault formula; ^+^ after Impella explantation; SAPS = Simplified Acute Physiology Score; ECG = Electrocardiography; TTE = Transthoracic echocardiogram; PAC = Pulmonary artery catheterization; NYHA = New York Heart Association; CCS = Canadian Cardiovascular Society; GCS = Glasgow coma scale; PCI = Percutaneous, coronary intervention; BGA = Blood gas analyses. EQ—5D = EuroQol questionnaire.

**Table 4 jcm-11-04623-t004:** Secondary endpoints of the JenaMACS study.

Secondary Endpoints
- Change of hemodynamic and echocardiographic parameters after 10 min, 30 min and every 8 h of Impella support - Need, type, dose and duration of inotropic/vasopressor treatment. - Time until hemodynamic stabilization (lactate < 2 mmol/L; mean arterial pressure > 65 mmHg) after implantation. - Change in inflammatory parameters over time. - Mean and area under the curve of serum-lactate measured every 8 h for 48 h after implantation. - Mortality defined as mortality rate in the hospital or anywhere after discharge, within 12 months after implantation. - Changes in kidney function after implantation. - Need and duration of renal replacement therapy (CVVHD) and mechanical ventilation after implantation. - Length of stay at ICU after implantation. - Need for an active assist device or heart transplantation after implantation. - SAPS II Score at baseline and every 24 h during Impella CP^®^ support. - EQ-5D-questionnaire including EQ VAS after implantation. - Neurological outcome (GCS) after implantation. - Safety aspects such as major bleeding according to GUSTO/BARC definition, critical limb ischemia, sepsis, hemorrhagic or ischemic stroke

CVVHD = continuous veno-venous hemodialysis, ICU = intensive care unit, SPAS = Simplified acute physiology score, EQ—5D = EuroQol questionnaire, VAS = Visual analogue scale, GCS = Glasgow Coma Scale BARC = Bleeding academic research consortium, GUSTO = Global use of streptokinase and t-PA for occluded coronary arteries, PCT = procalcitonin.

**Table 5 jcm-11-04623-t005:** Safety of the JenaMACS trial. Any of the mentioned adverse events (AE) is considered as a serious adverse event (SAE) if it is directly caused, may have caused in the past or may cause in the future death or a serious aggravation of the state of health of a patient, user or another person if the incident was caused by the medical device. The events will be recorded from the moment the medical device is unpacked and inserted into the patient until follow-up at discharge.

Safety of the Trial
- Peri-procedural complications within 7 days combined from: pericardial effusion, stroke, major bleeding, embolization, intracranial bleeding. - Device related: thrombus, breakage, malfunction, allergic reactions. - Vascular access related complications requiring intervention/surgery. - Procedure related death. - Post-procedure infection rate. - Sepsis with clinical signs of infection and increased PCT (>2 pg/mL). - Peri-procedural outcomes at 7 and 30 days after implantation. - Bleeding requiring transfusion (BARC 2—5). - Severe and moderate bleeding complications (GUSTO definition). - Stroke. - Severe limb ischemia/peripheral vascular complications.

BARC = Bleeding academic research consortium, GUSTO = Global use of streptokinase and t-PA for occluded coronary arteries, PCT = procalcitonin.

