#### 2.12.4. Post-Implantation

The patients are monitored until they are transferred to the intensive care unit. The flow of the device should be optimized according to clinical goals (MAP ≥ 65 mmHg).

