#### 2.12.5. Supportive Therapy in the Intensive Care Unit

Further intensive medical therapy is carried out according to generally recognized guidelines. Systemic anticoagulation with unfractionated heparin will be used for the duration of left ventricular support (target activated clotting time around 180 s).

Drug therapy with catecholamines (noradrenaline, dobutamine, possibly suprarenin, vasopressin) according to current recommendations is possible. The use of calcium sensitizers (e.g., levosimendan) or other hemodynamically relevant drugs (e.g., PDE inhibitors) are also possible according to an individual intensive care medicine assessment [14]. The aim, independent of the study, is to achieve a mean arterial blood pressure of at least 65 mmHg. All patients receive an invasive hemodynamic measurement using a standard pulmonary artery catheter. The daily doses of catecholamines and other hemodynamic drugs are documented. Furthermore, the daily fluid balance/management up to the explanation are recorded. If the use of a renal replacement therapy is necessary, the duration and type of the procedure are documented. In addition, the duration of any mechanical ventilation, the time of extubation and any reintubation that may be necessary are documented. Left ventricular ejection fraction is determined again within 24 h and after 7 days.

As part of the recording of the intensive medical treatment, the SAPS (Simplified acute physiology score) II score is recorded serially every day in the intensive care unit. To determine inflammatory parameters, as well as liver and kidney functions, a full blood work-up is recorded daily including C-reactive protein (CRP) and procalcitonin (PCT). All other laboratory parameters are determined at least once a day according to the documentation sheets in the routine laboratory program. Ethylenediaminetetraacetic acid (EDTA), blood, serum and plasma are stored at all times (before, after implantation, day 1–3 and 7) for later molecular biological analysis.

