#### 2.12.7. Weaning and Explantation of the Impella CP^®^ Device

The duration of therapy is determined by the need for supportive therapy with catecholamines. In previous studies, the mean duration of mechanical circulatory support was 3–4 days [21]. The main criterion for starting weaning from mechanical circulatory support is sustained hemodynamic stability (systolic RR > 90 mmHg for >60 min) without therapy with catecholamines and without signs of peripheral end-organ hypoperfusion. Impella^®^ flow is reduced in steps every 3 h; after 3 h at level 2, another echocardiography, hemodynamic measurement and blood sampling followed by explanation of the Impella^®^ take place. Standardized femoral artery access site closure takes place after explantation via a suture mediated percutaneous system as a first option (Perclose ProGlide^®^, Abbott laboratories, Abbott Park, Chicago, IL, USA)

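### The Table 4 stabilization event can already be met before implantation, and Table 3 uses the same word for a visit after explantation

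*Protocol article*

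**What the plan says.** Table 4 of the protocol article gives the secondary endpoint as "Time until hemodynamic stabilization (lactate < 2 mmol/L; mean arterial pressure > 65 mmHg) after implantation". It attaches no condition on drugs or pump support, and does not mention patients who meet the thresholds beforehand. Section 2.11.2 assigns time-to-event endpoints to Kaplan-Meier estimation.

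On entry, Table 1 states the pressure criterion as "Systolic blood pressure < 90 mmHg, >30 min of inotropic agents and/or vasopressors to keep the blood pressure > 90 mmHg systolic". It adds pulmonary congestion and "Signs of end-organ hypoperfusion with at least one of the following criteria". The four signs are somnolence, cold or pale skin or extremities, oliguria, and "Serum lactate > 2.0 mmol/L".

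On care during support, Section 2.12.4 sets pump flow with a MAP goal of 65 mmHg or more. Section 2.12.5, which allows catecholamines, says "The aim, independent of the study, is to achieve a mean arterial blood pressure of at least 65 mmHg".

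In Table 3, the column headed Stabilization carries a footnote placing it after removal of the pump. The Day 3-X column is footnoted "every day until hemodynamic stabilization". Section 2.12.7 starts weaning on "sustained hemodynamic stability (systolic RR > 90 mmHg for >60 min) without therapy with catecholamines", together with absence of hypoperfusion signs.

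**The concern.** A time-to-event endpoint needs patients who have not had the event at time zero. Here the entry criteria and the event definition overlap, so some patients may start with the event present. The MAP half of the event is also almost exactly the value that treatment is steered to, so it says little beyond whether care reached its target.

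The abstract names time to hemodynamic stabilization as an example of a clinical endpoint, and Section 2.6.2 wants the secondary measures to show or confirm possible advantages of the device. There is no comparison group, so the absolute time is the result. Events at time zero go straight into it, and no control arm shares the bias.

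The second problem is the word itself. If Table 3 is read with the Table 4 meaning, daily visits from Day 3 on could end while the pump is still running.

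**Working it through.** The document gives no event count, expected time or power for this endpoint, and Section 2.11.1 gives 20 patients without further inputs. There is no stated figure to reproduce. The check is whether the definitions overlap, and what follows if they do.

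**1. Overlap of entry and event**

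Assumption, not in the document: MAP = (SBP + 2 × DBP) / 3. MAP above 65 mmHg then requires DBP > (195 − SBP) / 2.

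| SBP (mmHg) | DBP must exceed (mmHg) | MAP at DBP 55 (mmHg) |
|---|---|---|
| 88 | 53.5 | 66.0 |
| 91 | 52.0 | 67.0 |
| 95 | 50.0 | 68.3 |
| 100 | 47.5 | 70.0 |

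Take a patient with pulmonary congestion, cold extremities and lactate 1.8 mmol/L, on vasopressors at 95/55 mmHg. MAP = (95 + 110) / 3 = 68.3. Table 1 is met through the skin sign, and both Table 4 thresholds are met before implantation. The 88 mmHg row shows that the overlap does not depend on the drug-supported part of the pressure criterion.

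**2. How many such patients**

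The document gives no share, so a range is assumed. With share p and 20 patients, the expected number is 20p and the chance of at least one is 1 − (1 − p)^20.

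| Assumed share | Expected of 20 | Chance of at least one |
|---|---|---|
| 5% | 1 | 0.64 |
| 10% | 2 | 0.88 |
| 20% | 4 | 0.99 |
| 30% | 6 | > 0.99 |

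**3. Effect on the reported median**

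Ignore censoring and let k of 20 patients have the event at time zero. The median over all 20 is reached at the 10th event, which is event 10 − k among the 20 − k patients who were truly at risk.

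- k = 1: 9/19 = 47%
- k = 2: 8/18 = 44%
- k = 4: 6/16 = 38%
- k = 6: 4/14 = 29%

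The reported median is then the time by which that smaller fraction of the at-risk patients had stabilized, so it is shorter than their own median.

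**4. The word in Table 3, set against other sections**

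- Table 4 meaning: reachable on drugs and pump, from time zero onward.
- Table 3 column: a visit after explantation.
- Table 3, Day 3-X footnote: ends the daily visits at stabilization without saying which meaning applies.
- Section 2.6.2: serial hemodynamic measurement continues until the pump is removed.
- Section 2.12.2: echocardiography is daily until explantation.
- Table 4, first item: measurements every 8 h of support.

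Read with the column's own meaning, the footnote agrees with the last three. Read with the Table 4 meaning, it conflicts with all three for any patient who reaches the thresholds while still on the pump.

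**The case against.** The case on the other side has real weight.

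- **On-support target.** Reaching lactate and MAP targets on the device is a fair question in a study of device support. A reader might infer that the endpoint fails because it does not measure recovery. No section says it measures recovery off support. In patients with raised baseline lactate it still captures lactate clearance under support. Drug need, dose and duration are a separate Table 4 endpoint, so heavy drug support would be visible in the report.
- **Weaning criterion.** A reader might count Section 2.12.7 as a third, rival definition. It is a criterion for starting weaning, and a different condition there does not contradict an endpoint. The firm conflict is between Tables 3 and 4.
- **Lost data.** A reader might infer that assessments would stop within hours of implantation. They would not. Day 1 and Day 2 are fixed columns, the footnote governs only Day 3-X, and Sections 2.6.2, 2.12.2 and 2.12.6 continue measurement in the ICU.
- **Size of the gap.** A reader might set 0–8 h for the Table 4 event against the 3–4 days of mean support cited in Section 2.12.7, giving 72 − 8 = 64 h to 96 − 0 = 96 h. That compares the earliest possible time with a mean from earlier studies, so it does not estimate a difference in any one patient.
- **Level of detail.** Rules on confirming a reading belong to an analysis plan, and silence on them is not a fault here.
- **Rarity.** Sections 2.3 and 2.4 restrict entry to patients needing mechanical support, judged on hemodynamics that include MAP. No cut-off is given. The example patient may be uncommon.

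What remains is the overlap between two stated definitions and the two meanings of one term. Neither is an omission.

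**Conclusion.** The point holds in limited form. Eligible patients can meet the Table 4 event before implantation, and as written they count as stabilized at time zero and shorten the reported time. The size cannot be fixed from the document: each such patient is 1 of 20, and the shares of 5% to 30% are illustrations. The overlap rests on the usual MAP formula and on reading Table 1 literally, with one hypoperfusion sign sufficient.

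The terminology conflict between Table 3 and Table 4 is certain from the text. Its practical effect is confined to visits from Day 3 on, and other sections already point to explantation as the end.

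This is one descriptive secondary endpoint. The primary ramp-test endpoint at 24 h is not touched. The change is worth making but is not critical to the study.

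**What to change.** 1. Analyse time to the Table 4 event only in patients who do not meet both thresholds at the pre-implantation reading. Report the others as a count out of all patients treated.
2. Name the endpoint as lactate/MAP target reached on support, so that it is not read as recovery off support.
3. In Table 3, rename the Stabilization column as after explantation. Reconcile the Day 3-X footnote with Sections 2.6.2 and 2.12.2 so that daily assessments run until explantation.
4. The sponsor should reconcile the stability wording of Section 2.12.7 with these terms. No clinical threshold is proposed here.

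A version requiring freedom from catecholamines or a confirmed second reading may be added as a sensitivity analysis, but is not required. It would be a different endpoint.

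The cost is wording. The baseline values are already collected: Table 3 schedules lactate and hemodynamics before PCI, and Section 2.12.1 records mean pressure before implantation. With k patients set aside, the at-risk set falls from 20 to 20 − k, and the reported time becomes longer.

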#### 2.12.8. 30 Day Follow-Up

A new echocardiographic assessment is carried out before discharge from the hospital. After 30 days, the patient’s vital status is again ascertained through contact. All clinical events are verified by obtaining the original documentation. In addition, dyspnea according to the New York Heart Association (NYHA)-classification, angina pectoris according to the Canadian Cardiovascular Society (CCS)-classification and quality of life according to the EuroQol (EQ)-5D questionnaire are recorded.

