### 2.13. Methods against Bias

#### 2.13.1. Blinding and Treatment Bias

Blinding is not possible because of the intervention used. Methods used against bias are standardized examination protocols to even out systematic differences due to differing expertise at all levels, and an independent clinical endpoint committee to evaluate adverse events other than death; high clinical standards are maintained with regard to the number of PCIs performed/year (about 1000) of patients treated in cardiogenic shock and participation in clinical studies. Furthermore, our study center has a certified, cardiac ICU specialized in the treatment of cardiac shock and application of Impella CP^®^ that are embedded in a quality management system. Investigators are trained in good clinical practice (GCP). All medical professionals involved are qualified and hold the appropriate national diploma or at least operate under surveillance of a senior staff member.

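### Table 5 stops safety recording at discharge but lists a 30-day outcome, so 30-day event counts can be incomplete for patients who leave hospital before day 30

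*Protocol article*

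**What the plan says.** Table 5 governs safety. Its caption sets the recording window: "The events will be recorded from the moment the medical device is unpacked and inserted into the patient until follow-up at discharge". Its items include one with a 30-day horizon, "Peri-procedural outcomes at 7 and 30 days after implantation", and a composite with a shorter one, "Peri-procedural complications within 7 days combined from: pericardial effusion, stroke, major bleeding, embolization, intracranial bleeding". It also lists "Procedure related death" and defines sepsis as "Sepsis with clinical signs of infection and increased PCT (>2 pg/mL".

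Section 2.12.8 plans a contact at 30 days: "After 30 days, the patient’s vital status is again ascertained through contact". It continues: "All clinical events are verified by obtaining the original documentation". NYHA class, CCS class and EQ-5D are collected at the same time. Table 3 schedules examinations at 30 days but has no row for adverse events at any visit.

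Section 2.13.1 lists, among the measures against bias, "an independent clinical endpoint committee to evaluate adverse events other than death".

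Table 4 names bleeding, limb ischemia, sepsis and stroke as secondary safety endpoints without a time window, and counts deaths from any cause to 12 months. Section 2.11.2 promises that safety events will be tabulated with 95% confidence intervals. Section 2.11.1 plans 20 patients.

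**The concern.** A 30-day event rate needs every patient to be observed for events until day 30 or death. The caption of Table 5 instead ends observation at a date that differs between patients. Someone still in hospital on day 30 has a full window, and so does someone who dies in hospital earlier. Someone discharged alive before day 30 does not, and a stroke, bleed or access-site complication after discharge falls outside the stated rule. Any loss would therefore fall on the patients who leave earliest, and the reported rate would mix full and truncated windows.

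Two smaller matters affect how events in the same table are classified. Calling a death procedure-related is a judgement on cause, and the independent committee's stated remit does not reach it. The PCT cut-off is printed in a unit that may not be the laboratory's.

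**Working it through.** The article states no safety rate and derives no sample size, so there is no figure to reproduce. The check compares the texts and then shows the scale.

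**1. The window.** Let d be the day of discharge alive. Under the caption, recording ends at d. For the 30-day item, the unrecorded days are 30 − d if d < 30, and none otherwise. The documents give no discharge times; for illustration only, d = 12 leaves 30 − 12 = 18 days. The 7-day items are affected only if d < 7.

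**2. Does the 30-day contact resolve it?** There are two readings of Section 2.12.8.
- It captures new events since discharge. Then it contradicts the caption of Table 5.
- It verifies only events already recorded. Then the 30-day item cannot be completed for early discharges.

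Neither reading removes the need to reconcile the passages. Table 3 does not decide between them, because it has no adverse-event row.

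**3. Scale at N = 20.** One patient is 1/20 = 5 percentage points. Exact (Clopper-Pearson) 95% intervals:
- 0/20 = 0% (0 to 16.8%)
- 1/20 = 5% (0.1 to 24.9%)
- 2/20 = 10% (1.2 to 31.7%)

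The documents give no rate of events between discharge and day 30. If a fraction q of patients has one (assumed), the chance of at least one in 20 patients is 1 − (1 − q)^20:
- q = 2%: 1 − 0.98^20 = 33%, with 20 × 0.02 = 0.4 expected
- q = 5%: 1 − 0.95^20 = 64%, with 1 expected
- q = 10%: 1 − 0.90^20 = 88%, with 2 expected

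Such events would be lost only if the discharge cut-off is applied literally and the 30-day contact does not feed the safety tables.

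**4. Death.** Table 4 counts deaths in hospital or afterwards to 12 months, so all-cause mortality depends neither on the Table 5 window nor on adjudication. Only the procedure-related count needs a causal judgement. The article names nobody to make it and gives no rule for it.

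**5. PCT unit.** 2 pg/mL ÷ 1000 = 0.002 ng/mL. If the laboratory reports in pg/mL, the cut-off works as printed. If it reports in ng/mL (assumption) and its lowest reportable value lies between 0.02 and 0.1 ng/mL (also an assumption), that value is already 0.02/0.002 = 10 to 0.1/0.002 = 50 times the cut-off. Any reportable result would then meet the PCT criterion.

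**The case against.** The best defence is that the article plans more than the caption suggests. There is a 30-day contact with verification from original records. Table 3 schedules a physical examination, ECG, echocardiography and neurological assessment at 30 days, and follow-up runs to 12 months. Only one item in Table 5 carries a 30-day horizon. The safety analysis is a description within a 20-patient, single-arm proof-of-concept study. Committee procedures are also commonly left to a full protocol that is not shown here.

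Much of this stands, and it rules out several stronger readings that a reader might draw:
- That the safety counts will be wrong. The 30-day contact may well catch later events; the text supports only that 30-day counts can be incomplete.
- That many deaths escape scrutiny. Applying the 30–70% mortality in the Introduction gives 20 × 0.30 = 6 to 20 × 0.70 = 14 deaths, but these are deaths from any cause, which need no adjudication. How many would raise a question of procedural cause is unknown.
- That the treating team will decide attribution. The article does not say who will. With one arm there is no allocation to blind, so the issue is independence.
- That every error makes safety look better. Missed late events lower the counts, whereas a PCT cut-off that is too low would raise the sepsis count. Sepsis also requires clinical signs of infection, so a criterion would remain.

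The defence does not remove the contradiction within Table 5. An article may omit detail, but here it prints a recording rule that one of its own listed outcomes cannot satisfy.

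**Conclusion.** The contradiction is real and should be settled before events are counted. As written, the discharge cut-off does not support the 30-day outcome in the same table, and 30-day counts can be incomplete for patients discharged before day 30. Each affected patient shifts a rate by 5 percentage points at N = 20. How many there would be is unknown; the 33%, 64% and 88% figures rest on assumed rates and a literal reading of the cut-off. The effect is confined to the safety description.

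The two secondary points are smaller. The gap in the committee's remit concerns the attribution of deaths, not whether they are recorded. The PCT point is a unit query: the conversion is certain, but the consequence (a criterion that hardly discriminates, and sepsis tending to be over-counted) depends on the laboratory reporting in ng/mL and on the assumed reporting limits.

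**What to change.** - Change the caption of Table 5 so that all its events are recorded to day 30 after implantation for every patient, or to discharge if that is later.
- State in Section 2.12.8 that the 30-day contact asks about new events since discharge and that these, once verified from source documents, enter the safety tables. Add an adverse-event row to Table 3.
- Extend the existing committee's remit in Section 2.13.1 to the attribution of deaths to the procedure or device. All-cause mortality needs no adjudication.
- Check the PCT unit in Table 5 against the laboratory's reporting unit before any sepsis is classified, and correct the print if they differ.

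The cost is wording in the protocol and case report form, a few more questions at a contact already planned, and some added work for a committee that already exists. For anyone already enrolled, the 30-day information would have to be completed from existing records. Counts of late events may rise; if the PCT unit proves to be a misprint, the sepsis count may fall.
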